## Abstract

**Background:**

Alterations in intestinal microbiota correlate with risk of development of obesity and type 2 diabetes. Probiotics have been suggested to play an important role in the management of dysglycemia, although the evidence is limited. In this study, we aim to explore the efficacy and safety of probiotics intervention in preventing type 2 diabetes in Chinese patients with impaired glucose tolerance.

**Methods/Design:**

A 24-month randomized intervention is conducted from January 2014 to December 2016. The target sample size for intervention is 200 middle-aged men and women aged 30–65 year-old with impaired glucose tolerance. Participants with persistent impaired glucose tolerance were assigned to group A (tablet A) and B (tablet B) in sequential order. The participants and investigators were blinded to the assignment. The primary outcome is development of diabetes. The secondary outcome measures include body composition, biochemical variables and the safety of the probiotics.

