## Methods/Design

### Trial design

The PPDP is a 24-month, double-blinded, two-arm parallel group trial. Participants are individually randomized to one of two intervention groups in a 1:1 allocation. Participants are recruited from the outpatient department of five clinical centers in Shanghai during 2014 to 2016. They are Shanghai East Hospital, Shanghai Fifth People’s Hospital, Xinhua Hospital, Chongming Branch, Shanghai Pudong Hospital, Shanghai Seventh People’s Hospital. After an initial screening, potential subjects will be assessed for inclusion in the run-in trial. Those who meet the inclusion criteria are randomized to either intervention group or placebo group (Fig. 1).

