### Outcomes

#### Primary outcomes

The primary clinical outcome is the improvement of risk of developing diabetes after administration of probiotics for 24 months.

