#### Follow-up visits

The purpose of follow-up visits is to monitor the compliance and to discover the adverse events. After the first visit, a researcher will contact participants every month to check their medication. The participants will have follow-up visits to the clinical laboratory every 2 months. Their height, weight, waist circumference, hip circumference, blood pressure, heart rate and newly combined medication will be checked at those time points. In addition, at months 6, 12, 18, 24, participants will undergo a 75 g OGTT to evaluate the glycemic status (blood draw after 8 h overnight fasting and 30 min and 2 h after glucose load) and take blood samples and fecal samples (Table 1).

**Table 1 Tab1:** Visit study and efficacy variables for Probiotics Prevention Diabetes Programme (PPDP)

Visit number	1	2	3	4	5	6	7	8	9	10	11	12	13
Study month	0	2 m	4 m	6 m	8 m	10 m	12 m	14 m	16 m	18 m	20 m	22 m	24 m
Newly diagnosed diabetes(*n*)	×			×			×			×			×
OGTT + IRT(0 min,30 min,2 h)^a^	×			×			×			×			×
Total cholesterol	×			×			×			×			×
Triglyceride	×			×			×			×			×
High-density lipoprotein	×			×			×			×			×
Low-density lipoprotein	×			×			×			×			×
Body weight	×	×	×	×	×	×	×	×	×	×	×	×	×
Systolic blood pressure	×	×	×	×	×	×	×	×	×	×	×	×	×
Diastolic blood pressure	×	×	×	×	×	×	×	×	×	×	×	×	×
Waist circumference	×	×	×	×	×	×	×	×	×	×	×	×	×
Hip circumference	×			×			×			×			×
Abundance of bacteria	×			×			×			×			×
LPS	×			×			×			×			×
GLP-1	×			×			×			×			×

^a^OGTT, oral glucose tolerance test; IRT, insulin release test; LPS, lipopolysaccharides

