### Trial status

Participant recruitment started in September 2014. Baseline measurement started in October 2014 for the first enrolled subjects. Medicine interventions started in October 2014. The recruitment of subjects is continuing until October 2015.

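### The stated calendar does not fit 24 months of follow-up: only participants starting by December 2014 can reach month 24 before the stated end, yet recruitment runs to October 2015

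*Protocol article*

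**What the plan says.** All references are to the protocol article.

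**Calendar.** Three places give dates.
- Abstract, Methods/Design: "A 24-month randomized intervention is conducted from January 2014 to December 2016".
- Trial design: "Participants are recruited from the outpatient department of five clinical centers in Shanghai during 2014 to 2016".
- Trial status: "Participant recruitment started in September 2014", "Medicine interventions started in October 2014" and "The recruitment of subjects is continuing until October 2015".

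**Length of follow-up.** Trial design: "The PPDP is a 24-month, double-blinded, two-arm parallel group trial". Primary outcomes: "The primary clinical outcome is the improvement of risk of developing diabetes after administration of probiotics for 24 months". Follow-up visits: "at months 6, 12, 18, 24, participants will undergo a 75 g OGTT to evaluate the glycemic status". Table 1 has its last visit at month 24, and Sample size calculations states power at two years.

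**Analysis.** Statistical methods uses survival curves for the cumulative incidence of diabetes and a two-sided log-rank test between groups. The article mentions no common closing date, no shortened follow-up for late entrants and no extension.

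**The concern.** Treatment length, primary outcome, visit schedule and sample size all assume that each participant is followed for 24 months. The only stated end date does not allow this for anyone who starts in 2015.

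If that date governs, the later recruits leave the risk set before month 24 for purely administrative reasons. The 24-month end of the survival curve is then carried by the earliest recruits, and the trial has fewer events than the sample size section implies. If the date does not govern, the published end of study is wrong, and moving it later, once data have accumulated, could look data-driven. In either case a reader cannot tell from the article how long participants will be followed.

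**Working it through.** **1. Calendar (no assumption needed).**
- Latest start that allows 24 months by 31 December 2016: 31 December 2014.
- First treatment: October 2014. Last recruitment: October 2015.
- Month 24 of an October 2015 entrant: October 2017, about 10 months after the stated end.
- Follow-up available to the last entrant by 31 December 2016: 14 to 15 months, so the last scheduled test is at month 12.

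**2. The plan's own power figure.** Inputs from Sample size calculations: 100 per arm, 35% in the placebo group, a 14% difference (read as absolute, so 21%), two-sided 0.05.
- Two proportions: (0.14 − 1.96 × √(2 × 0.28 × 0.72/100)) / √((0.35 × 0.65 + 0.21 × 0.79)/100) = 0.25, which gives power of 60%.
- Log-rank: hazard ratio = ln(0.79)/ln(0.65) = 0.547. Events with full follow-up = 100 × 0.35 + 100 × 0.21 = 56. Power = Φ(√56 × |ln 0.547|/2 − 1.96) = Φ(0.296) = 62%.

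The stated 80% is not reproduced even with 24 months for everyone. Reading the figure as 35% versus 14% gives 94%, and as a relative 14% reduction 11%. The baseline for the calendar effect is therefore 62%.

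**3. Share without a possible month-24 test.** Assumption: uniform accrual, because the article gives no rate.
- Entry from 1 October 2014 to 1 October 2015: 75% cannot reach month 24.
- Entry from 1 October 2014 to 31 October 2015: 77% (154 of 200, or 169 of 220).
- Moving the first entry between 1 September and 31 October 2014, and the last between 1 and 31 October 2015: 69% to 83%.

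**4. Last test reached.** Entry at t months after 1 October 2014, closure at month 27, last test = min(24, 6 × ⌊(27 − t)/6⌋).

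| Last test | 12-month entry window | 13-month entry window |
|---|---|---|
| Month 24 | 25% | 23% |
| Month 18 | 50% | 46% |
| Month 12 | 25% | 31% |

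**5. Events and power if December 2016 is applied.** Assumptions: 200 participants, no dropout, constant hazards −ln(0.65)/24 and −ln(0.79)/24 per month. The cumulative risks (placebo, probiotics) are 19.4% and 11.1% at month 12, 27.6% and 16.2% at month 18, and 35% and 21% at month 24.

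For the 12-month window with detection at visits:
- Placebo: 0.25 × 35 + 0.50 × 27.6 + 0.25 × 19.4 = 27.4%.
- Probiotics: 0.25 × 21 + 0.50 × 16.2 + 0.25 × 11.1 = 16.1%.
- Events: 27.4 + 16.1 = 43.5.
- Power: Φ(√43.5 × 0.603/2 − 1.96) = 51%.

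| Detection | Events | Log-rank power |
|---|---|---|
| Full 24 months for all | 56 | 62% |
| At scheduled tests, closure December 2016 | 42.5 to 43.5 | 50% to 51% |
| Continuous, closure December 2016 | 48 to 49 | 55% to 56% |

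**6. Month-24 status unknown.** Some of those without a month-24 test will already have converted. With detection at visits, the share that is censored free of diabetes before month 24, averaged over the arms, is 60% (12-month window) to 62% (13-month window).

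**7. Sensitivity to accrual.** Suppose half of all participants enter in the first quarter of a 12-month window and the rest evenly afterwards. Then 50% still miss month 24 (33.3% stop at month 18, 16.7% at month 12). Events are 100 × (0.299 + 0.178) = 47.7 and power is 55%. The loss shrinks but remains.

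**The case against.** The strongest reply is that early closure is nowhere planned. December 2016 appears once, in the abstract, while every operative section commits each participant to 24 months. January 2014 to December 2016 is 36 months, which would fit 12 months of recruitment plus 24 of treatment, and Trial status reports treatment starting about nine months later than that window opens. A calendar that was not updated after a late start is at least as plausible as an intention to stop early, and on that reading no events are lost. This stands: the losses above are conditional on December 2016 being a true closing date. It does not remove the contradiction, because the article does not say which reading is meant.

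A reader might also infer that the primary outcome is unobservable for three quarters of participants. The documents do not support that. The analysis is time-to-event, so a participant closed out early is administratively censored and still contributes events and time at risk. Everyone can have the month-6 and month-12 tests, and about 69% to 75% the month-18 test. The log-rank test remains valid under such censoring.

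A reader might further take the recruitment years under Trial design literally and conclude that entry in 2016 makes matters worse. That phrase may only repeat the study years, and Trial status is the more specific statement. It is a reason to align the text, not evidence of a larger loss.

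**Conclusion.** The dates in the Abstract, Trial design and Trial status are incompatible with one another and with 24 months of follow-up for all. This part is certain and rests on no assumption.

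The size is conditional. If December 2016 is applied and accrual is uniform, about three quarters (69% to 83%) cannot have a month-24 test and month-24 status is unknown for about 60% to 62%. Expected events fall from 56 to about 43-49 and log-rank power from 62% to about 50-56%, depending on whether conversion is detected at visits or continuously. These figures take 200 participants, no dropout, constant hazards and an absolute difference of 14 points. Front-loaded accrual would reduce the loss.

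The calendar should not be blamed for the whole distance from the stated 80%. The fall from 80% to 62% exists with complete follow-up and is a separate problem. The calendar accounts only for the further 6 to 12 points.

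**What to change.** Choose one of two courses and state it before the study closes.

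1. Define the study end as the last participant's month-24 visit, which is October 2017 or later with recruitment to October 2015, and correct the abstract. Each participant then has the follow-up that the primary outcome and sample size assume. The cost is a date change in the protocol, and in any registry entry that carries the same date, plus about 10 more months of visits that are already scheduled in Table 1.

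2. Declare December 2016 a common closing date with staggered administrative censoring. Restate the expected events and power from the actual entry dates, and do not describe the result as a 24-month risk observed in all participants. The cost is a less favourable stated power and a 24-month estimate that rests on the earliest recruits.

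Under either course, make the recruitment years in Trial design agree with Trial status.

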**Discussion:**

The results from this trial will provide the evidence on the efficacy and safety of probiotics administration in preventing conversion of impaired glucose tolerance to diabetes in a Chinese context.

**Trial registration:**

ChiCTRTRC13004024

## Background

Diabetes has become a worldwide epidemic in the general population. In China, the prevalence of diabetes among adults is 11.6 % according to the data released in 2013 [1]. In addition, the prevalence of prediabetes is up to 50.1 %. Individuals with prediabetes, especially impaired glucose tolerance (IGT), are at higher risk of developing type 2 diabetes, compared with individuals with normal glucose tolerance.

Studies have shown that early intervention in patients with IGT can significantly reduce the number of those patients who subsequently develop type 2 diabetes [2–6]. Those effective interventions conclude lifestyle modification and drug therapy. The efficacy of lifestyle modification in preventing the conversion of IGT to type 2 diabetes is proven [2, 3]. Drug therapy such as metformin, alpha-glucosidase inhibitor and Thiazolidinediones, has also been proven useful in the primary prevention of diabetes in people with IGT [4–9]. However, in clinical practice, the compliance of using hypoglycemic drugs to reduce the incidence of diabetes for nondaibetic subjects in natural population is relatively low. So to find a kind of non-hypoglycemic agents, on the basis of lifestyle modification, to help preventing the conversion of IGT to diabetes for subjects with prediabetes will be meaningful.

Recent evidences suggest that alterations in gut microbiota play an important role in the pathogenesis of obesity-related disorders, including diabetes and non-alcoholic fatty liver disease [10–15]. Compared with germ-free mice, conventionally raised mice were more prone to obesity and insulin resistance [10]. In human studies, it also has shown that gut microbiota composition differs between obese and lean subjects [11]. Recent metagenome-wide association studies showed that patients with type 2 diabetes have an increase in the abundance of Lactobacillus species and decreases in the abundance of Clostridium species [12, 13]. Thus, reshaping the gut microbiome may be a new direction for the prevention and treatment of diabetes in human beings. Currently the published evidences of the treatment of metabolic diseases with probiotics are limited, and the results are inconsistent [16–19]. Some but not all trials suggest that probiotics consumption may improve blood glucose level and antioxidant status in type 2 diabetic patients [16]. Two trials showed that probiotics intervention only improved the lipid metabolism but not blood glucose in patients with diabetes or gestational diabetes mellitus [17, 18]. Only one trial explored the effects of probiotics administration on the outcomes of blood lipids and blood pressure in patients with prediabetes, but no data on the outcome of glucose metabolism [19]. In addition, the intervention period of those trials may be too short (4 to 8 weeks) to observe the effect of probiotics. To date there is no clinical trial to explore whether probiotics administration can reduce the risk of development of type 2 diabetes in patients with prediabetes.

Therefore, the purpose of this study is to investigate the efficacy and safety of probiotics administration in preventing the development of type 2 diabetes in subjects with IGT compared to placebo. In addition, we will determine probiotics administration improve insulin sensitive and metabolic variables. The secondary outcome measures include body composition, biochemical variables and the safety of probiotics.

## Methods/Design

### Trial design

The PPDP is a 24-month, double-blinded, two-arm parallel group trial. Participants are individually randomized to one of two intervention groups in a 1:1 allocation. Participants are recruited from the outpatient department of five clinical centers in Shanghai during 2014 to 2016. They are Shanghai East Hospital, Shanghai Fifth People’s Hospital, Xinhua Hospital, Chongming Branch, Shanghai Pudong Hospital, Shanghai Seventh People’s Hospital. After an initial screening, potential subjects will be assessed for inclusion in the run-in trial. Those who meet the inclusion criteria are randomized to either intervention group or placebo group (Fig. 1).

**Fig. 1 Fig1:**
[figure not shown]
Study design and participant flow diagram for Probiotics Prevention Diabetes Programme (PPDP)

### Participants

***Inclusion criteria are****:* (i) men or women aged 30–65 years; (ii) diagnose IGT after oral glucose tolerance test (OGTT) according to 1999 WHO criteria (fasting glucose <6.1 mmol/L, and 2-h post glucose load ≥ 7.8 and <11.1 mmol/L), (iii) no chronic cardiovascular, liver, kidney, lung diseases, (iv) informed consent, agreement on no other drug therapy on IGT during trial.***Exclusion criteria are****:* (i) patients with severe liver, kidney, heart, nervous system and gastrointestinal diseases, (ii) diagnosis of diabetes mellitus, (iii) allergy to studied agents, (iv) suspected or definite a history of alcohol or drug abuse history, (v) the possibility of loss to follow-up according to the judgment of the researchers, (vi) patients who have participated in other clinical trials in the past 3 months.

### Interventions

Eligible participants are randomly assigned in double-blind to receive either probiotics or placebo which are blinded as Tablet A and Tablet B for 24 months. The key that indentifies the subjects and which group they belong to is kept by a third party, and is not revealed to the researchers until the end of the study and the statistic analysis is finished. Probiotics are provided by Bifico (Approval number: S10950032), an over the counter capsule consists of live combined Bifidobacterium longum [National Center for Medical Culture Collections (CMCC): P0001], Lactobacillus acidophilus [CMCC: P0002] and Enterococcus faecalis [CMCC: P0003] produced by Shanghai Sine Pharmaceutical Laboratories Co,Ltd. The study drug and the placebo are prepared in indistinguishable tablets. For both group, the dose are 840 mg daily, 210 mg per one pill, two pills per time, two times daily (Fig. 1).

### Outcomes

#### Primary outcomes

The primary clinical outcome is the improvement of risk of developing diabetes after administration of probiotics for 24 months.

#### Secondary outcomes

(i) the cumulative prevalence of diabetes in the two groups, (ii) the changes of blood glucose, lipid profile and insulin sensitivity in the two groups, (iii) the changes of body weight and waist circumference, (iv) the safety assessment of probiotics, (v) the change of the abundance of gut bacteria, (vi) the change of blood lipopolysaccharides (LPS) and GLP-1 levels.

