#### First visit

Before the first visit, a physician examines all the results of the screening to verify whether the subject meets the inclusion criteria. In the first visit (within 1 week of the screening), if a person is qualified for participation in the study (fasting glucose <6.1 mmol/L, and 2-h post glucose load ≥7.8 and <11.1 mmol/L, with no other chronic diseases), he or she will be invited to the clinical laboratory of Department of Endocrinology, Shanghai East Hospital for height, weight, waist circumference and blood pressure measurement, as well as instructions for fecal sample. Then they will be randomized and assigned in double-blind to receive either probiotics or placebo for 8 weeks. We emphasize the importance of their participation in study and instruct them to take medicine on time during the intervention.

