#### Stool samples collection

The stool samples will be collected at the first visit and at months 6, 12, 18, 24. Detailed stool sample collection and transportation instructions will be given by a study researcher. We will provide to subjects the materials for sample collection and transportation from home to hospital which including: 1 cool box, 1 sterile dressing room, 1 sterile EP tubes, 1 pair of sterile tweezer, 1 pair of plastic gloves and a plastic bag. The participants are advised to sample approximately 5 g of feces by tweezer attached to the sterile EP tubes. Then the sterile EP tubes are stored in a plastic bag in the cool box. After samples are collected, the subjects will immediately deliver the samples to the clinical laboratory in 1 h.

The stool samples will be frozen at −80 °C after collected and the DNA extraction will be performed using the E.Z.N.A.^®^ Stool DNA Kit (Omega Bio-tek, Norcross, GA, U.S.) according to manufacturer’s protocols. Fecal bacteria composition will be determined using 16S rRNA based methods and illumina MiSeq sequencing.

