## Discussion

IGT is associated with progressing to diabetes and risk of cardiovascular diseases. Epidemiological studies showed that 25 % of patients with IGT progress to type 2 diabetes in 5 years [2] and the rate reach to 41 % in China [20]. An unhealthy diet and the alterations in gut microbiota play an important role in this process. Although the diet control is helpful to the prevention and treatment of diabetes, it is difficult for the individual to insist on. Recent studies showed that reshaping the gut microbiome can improve the energy metabolism [16–19, 22], which provide a new insight on preventing the occurrence of type 2 diabetes. Therefore, we present a design of a randomized double-blinded, placebo-controlled trial to investigate the efficacy and safety of probiotics intervention in preventing conversion of IGT to type 2 diabetes in China. To the best of our knowledge, this is the first study, in a relative larger sample and in a longer period, to evaluate the efficacy of probiotics administration on glucose metabolism in IGT subjects.

This trial has been designed to address the limitations of previous studies of the effects of probiotics administration on the outcomes of metabolic diseases. The duration of intervention and the sample size will allow us to explore the effects of probiotics intervention on metabolic diseases. We expect that the overall incidence of diabetes will be significantly reduced in probiotics group than placebo group, which suggest that type 2 diabetes can be prevented by oral administration probiotics for subjects at high risk for the disease. We also anticipate that probiotics intervention will improve insulin sensitivity, lipid profile, and inflammatory state by changing the gut microbiota composition.

This trial using oral administration of probiotics offers a new approach for both diabetes and metabolic diseases prevention. If the result of the research shown to be effective, it will open a new strategy for diabetes prevention.

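### Gut-bacteria outcome (v) does not separate swallowed product from change in the rest of the community, so a rise confined to the three product genera would not support the expected mechanism

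*Protocol article*

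**What the plan says.** **Outcome.** Item (v) under Secondary outcomes is "the change of the abundance of gut bacteria". No taxa are named and the administered organisms are not set apart. Statistical methods lists abundance of bacteria among the outcomes compared between arms by a baseline-adjusted mixed model at months 6, 12, 18 and 24, with a treatment-by-time interaction.

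**Product.** Interventions describes the product as "an over the counter capsule consists of live combined Bifidobacterium longum" together with Lactobacillus acidophilus and Enterococcus faecalis. It is taken twice daily: "the dose are 840 mg daily, 210 mg per one pill, two pills per time, two times daily".

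**Duration.** Interventions says participants "receive either probiotics or placebo which are blinded as Tablet A and Tablet B for 24 months". The Abstract, Trial design and Primary outcomes sections also give 24 months. The First visit section says they are "randomized and assigned in double-blind to receive either probiotics or placebo for 8 weeks".

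**Sampling and assay.** "The stool samples will be collected at the first visit and at months 6, 12, 18, 24"; Follow-up visits and Table 1 give the same times, with none later. "Fecal bacteria composition will be determined using 16S rRNA based methods and illumina MiSeq sequencing".

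**Intended conclusion.** The Discussion expects the intervention to "improve insulin sensitivity, lipid profile, and inflammatory state by changing the gut microbiota composition". The Background presents reshaping of the gut microbiome as the route to prevention. It names two taxa linked to type 2 diabetes: Lactobacillus, reported as increased, and Clostridium, reported as decreased.

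**The concern.** Sequencing of stool DNA counts whatever bacterial DNA is in the stool. In a participant taking live bacteria every day, that can include DNA from the tablets in transit, from living or dead cells, as well as DNA from residents of the same genera. If the samples are taken during dosing and the outcome covers all gut bacteria without distinction, a between-arm difference in Bifidobacterium, Lactobacillus or Enterococcus can arise simply because one arm swallowed those organisms.

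Neither the placebo comparison nor the baseline adjustment removes this. The baseline stool precedes dosing and the placebo arm receives none of the organisms, so the product's own DNA lies entirely in the treatment contrast.

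What is at stake is the mechanism. The Discussion expects metabolic benefit through an altered microbiota. A difference that reflects only intake could be reported as support for that pathway. One of the two taxa that the Background links to diabetes, Lactobacillus, is a product genus and so directly exposed to this. A secondary effect follows from read proportions summing to one: extra product reads make every other taxon look slightly scarcer.

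**Working it through.** The plan states no figure on this point, so there is none to reproduce. The check sets the schedule against the dosing period and then illustrates the size.

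**1. Schedule against dosing**

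| Dosing text | Section | Follow-up stools within or at the end of dosing | After dosing |
|---|---|---|---|
| 24 months | Abstract, Trial design, Interventions, Primary outcomes | 4 of 4 | 0 of 4 |
| 8 weeks | First visit | 0 of 4 | 4 of 4 (the first about 4 months after dosing ends) |

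The concern therefore applies under the 24-month text and not under the 8-week text.

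**2. What product DNA does to read proportions**

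Both inputs are assumptions, because the documents give neither:
- b: share of reads from the three product genera at baseline, taken as 1% or 5%;
- s: share of on-dose reads that come from the product, taken as 0.1%, 1% or 5%.

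The resident community is held unchanged.

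- On-dose share of product genera = (1 − s)b + s
- Fold change = [(1 − s)b + s] / b
- Any other genus with baseline share a becomes a(1 − s), a relative fall of s

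Example with b = 1% and s = 1%: 0.99 × 0.01 + 0.01 = 0.0199, and 0.0199 / 0.01 = 1.99.

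| b | s | On-dose share of product genera | Fold change | Relative change in every other genus |
|---|---|---|---|---|
| 1% | 0.1% | 1.099% | 1.10 | −0.1% |
| 1% | 1% | 1.99% | 1.99 | −1% |
| 1% | 5% | 5.95% | 5.95 | −5% |
| 5% | 0.1% | 5.095% | 1.02 | −0.1% |
| 5% | 1% | 5.95% | 1.19 | −1% |
| 5% | 5% | 9.75% | 1.95 | −5% |

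**3. What product DNA cannot do**

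For two non-product genera with baseline shares a1 and a2, the on-dose ratio is a1(1 − s) / [a2(1 − s)] = a1 / a2. Their relative make-up does not move.

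If the product genera are removed and proportions recomputed, the remaining total is 1 − [(1 − s)b + s] = (1 − s)(1 − b). A non-product genus then has share a(1 − s) / [(1 − s)(1 − b)] = a / (1 − b), which is its recomputed baseline value whatever s is. Removing the three genera thus cancels both the direct rise and the dilution. A between-arm difference that remains is not produced by product reads.

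**The case against.** **This is a one-line outcome in an article.** Which taxa are modelled, how proportions are normalised and whether product genera are reported apart are commonly left to a fuller plan, which may well deal with them. No section sets a target taxon or a success rule for (v), so a reader should not infer that the plan declares a rise in product genera a positive result. That stands, and it limits the strength of the point. What remains is that the article itself fixes the sampling times, the assay, an undifferentiated outcome and the mechanism to be supported, and these together leave intake and community change unseparated.

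**The standard of resident change is imported.** The article speaks of changing composition, does not exclude the administered organisms and does not promise persistence after dosing. Measuring stool at the same visits as the OGTT, lipids, LPS and GLP-1 is coherent. This stands too, and no washout sample is asked for. But language about reshaping the microbiome goes beyond detecting in stool the organisms that were swallowed.

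**A stronger reading fails.** A reader might infer that the trial cannot show any reshaping of the resident microbiota. The documents do not support this. Taxa outside the product, including Clostridium, can be compared with placebo in the same sequence data. Nor do they support calling a rise in the product genera near certain, since they give no viable count or read share.

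**The duration is contradictory.** The 8-week statement in First visit would remove the premise, so the point must be stated as conditional on the 24-month text.

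**Conclusion.** The point holds in limited form. Under the 24-month dosing text, outcome (v) as worded does not distinguish product intake from change in the rest of the gut community, and a rise confined to Bifidobacterium, Lactobacillus and Enterococcus would not support the mechanism that the Discussion expects.

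The size is unknown. In the illustration, passenger DNA alone raises the product genera 1.02-fold to 5.95-fold, whereas the distortion of any other genus is only 0.1% to 5% in relative terms and ratios among the others do not move. The problem is therefore concentrated in the three product genera.

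This rests on three assumptions: that dosing lasts 24 months, that product DNA reaches the stool in measurable amounts, and that the 16S read does not identify the source of organisms within a genus. It concerns one of six secondary outcomes. The primary diabetes comparison is unaffected.

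**What to change.** 1. Reconcile the treatment duration in First visit with that in the Abstract, Trial design, Interventions and Primary outcomes sections, and state when each stool is taken relative to dosing.
2. Keep the all-taxa description of (v), and add a prespecified between-arm analysis in which reads of the three product genera are removed and proportions recomputed, using the mixed model and time points already planned.
3. Report the three product genera separately, interpreted as possibly reflecting intake, beside the returned tablet counts described under Treatment compliance.
4. Base any conclusion about reshaping the microbiota on the non-product analysis.

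The cost is outcome wording and analysis on sequence data already being collected, with no new samples or visits. The downside is that true resident changes within the three genera, including Lactobacillus named in the Background, would not count toward that conclusion, although they would still be reported.
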